#### 3.2 Penn Medicine BioBank (Primary Cohort)

PMBB is an EHR-linked biobank at the University of Pennsylvania with >40,000 participants, ~30% non-European ancestry. We will identify all African-American PMBB participants with APOL1 high-risk genotype (two risk alleles: G1/G1, G2/G2, or G1/G2), age ≥18, and baseline eGFR >60 mL/min/1.73m^2. APOL1 genotype was determined via whole-exome sequencing (Regeneron) or equivalent genotyping. Plasma proteomic profiles (7,549 proteins) were measured at baseline using the SomaScan aptamer platform. We have identified 1,113 eligible participants for the primary cohort (expanded from 550 in the prior dataset). Additional CKD participants with APOL1 high-risk genotype and 967 African ancestry APOL1 low-risk participants (267 newly added) and 698 European ancestry APOL1 low-risk were included as external reference. Baseline covariates include age, sex, eGFR (CKD-EPI 2021), and albumin-to-creatinine ratio (UACR). To better enable comparison between the African ancestry APOL1 high-risk and low-risk groups, propensity score matching was applied using age, sex, eGFR, UACR, diabetes, hypertension, and cardiovascular disease, with separate matching performed for participants with eGFR >60 and ≤60 mL/min/1.73 m^2 (Appendix 1 to 3).

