**Appendix 1 Propensity score matching for APOL1 high-risk and APOL1 low-risk with eGFR>60 cohort**

|                                              | APOL1 high-risk | APOL1 low-risk |         |                           |         |
|----------------------------------------------|-----------------|----------------|---------|---------------------------|---------|
|                                              |                 | Initial cohort |         | Propensity score matching |         |
| Number                                       | 851             | 944            | P value | 874                       | P value |
| Age - yr                                     | 49.22±15.07     | 50.37±13.81    | 0.09    | 49.9±14.03                | 0.33    |
| Female - no. (%)                             | 566(66.51%)     | 610(64.62%)    | 0.4     | 568(64.99%)               | 0.51    |
| SBP - mmHg                                   | 128.54±17.79    | 129.34±17.46   | 0.34    | 129.3±17.41               | 0.37    |
| DBP- mmHg                                    | 77.59±11.9      | 77.51±11.44    | 0.88    | 77.42±11.47               | 0.76    |
| Body Mass Index - kg/m           | 32.27±7.84      | 32.06±7.82     | 0.57    | 32.29±7.83                | 0.95    |
| Hemoglobin A1c (%)                           | 6.57±1.81       | 6.36±1.36      | 0.11    | 6.39±1.39                 | 0.19    |
| Creatinine (mg/dL)                           | 0.88±0.21       | 0.84±0.19      | <0.01   | 0.86±0.18                 | 0.07    |
| Blood Urea Nitrogen (mg/dL)                  | 13.04±4.98      | 12.44±4.34     | <0.01   | 12.56±4.39                | 0.03    |
| eGFR - ml/min/1.73m              | 90.59±17.04     | 93.04±16.38    | <0.01   | 91.96±16.39               | 0.09    |
| UACR (IQR) - mg/g                            | 17.23(11-31)    | 15.31(12-24)   | 0.02    | 15.31(12-24)              | 0.05    |
| 30~299 - no. (%)                             | 112(13.16)      | 153(16.21)     |         | 138(15.79)                |         |
| ≥ 300 - no. (%)                              | 25(2.93)        | 24(2.54)       |         | 23(2.63)                  |         |
| Red Blood Cells (×10  /μL)       | 4.32±0.63       | 4.35±0.61      | 0.43    | 4.34±0.61                 | 0.44    |
| White Blood Cells (×10  /μL)     | 7.36±3.46       | 7.21±3.08      | 0.32    | 7.21±3.12                 | 0.33    |

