**Appendix 2 Propensity score matching for APOL1 high-risk and APOL1 low-risk with eGFR≤60 cohort**

|                                              | APOL1 high-risk | APOL1 low-risk |         |                           |         |
|----------------------------------------------|-----------------|----------------|---------|---------------------------|---------|
|                                              |                 | Initial cohort |         | Propensity score matching |         |
| Number                                       | 262             | 51             | P value | 38                        | P value |
| Age - yr                                     | 57.73±15.84     | 54.68±14.61    | 0.2     | 55.41±15.38               | 0.4     |
| Female - no. (%)                             | 135(51.53%)     | 36(70.59%)     | 0.01    | 25(65.79%)                | 0.1     |
| SBP - mmHg                                   | 130.87±19.81    | 131.84±17.66   | 0.74    | 133.55±18.5               | 0.43    |
| DBP- mmHg                                    | 75.23±12.26     | 79.04±12.18    | 0.04    | 78.75±13.7                | 0.08    |
| Body Mass Index - kg/m           | 30.93±7.58      | 32.0±8.56      | 0.37    | 32.71±8.39                | 0.18    |
| Hemoglobin A1c (%)                           | 6.66±1.81       | 6.03±0.88      | 0.19    | 6.37±0.86                 | 0.63    |
| Creatinine (mg/dL)                           | 1.99±0.95       | 1.56±0.79      | <0.01   | 1.68±0.87                 | 0.06    |
| Blood Urea Nitrogen (mg/dL)                  | 28.69±14.44     | 25.27±13.93    | 0.12    | 27.63±15.33               | 0.67    |
| eGFR - ml/min/1.73m              | 38.19±16.67     | 45.99±14.5     | <0.01   | 43.46±15.97               | 0.07    |
| UACR (IQR) - mg/g                            | 31.67(15-124)   | 17.23(12-45)   | 0.14    | 24.12(12-62)              | 0.26    |
| 30~299 - no. (%)                             | 51(20.23)       | 12(23.53)      |         | 11(28.95)                 |         |
| ≥ 300 - no. (%)                              | 35(13.89)       | 5(9.80)        |         | 5(13.16)                  |         |
| Red Blood Cells (×10  /μL)       | 3.98±0.7        | 4.08±0.67      | 0.37    | 4.01±0.7                  | 0.79    |
| White Blood Cells (×10  /μL)     | 7.44±3.54       | 7.56±2.87      | 0.83    | 7.73±2.87                 | 0.63    |

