| Total Bilirubin (mg/dL)                      | 0.66±0.46       | 0.75±0.63      | 0.22    | 0.74±0.59                 | 0.33    |
| Prothrombin Time (sec)                       | 15.78±7.56      | 14.72±5.36     | 0.55    | 14.73±6.15                | 0.62    |
| Activated Partial Thromboplastin Time (sec)  | 32.87±13.72     | 29.35±3.87     | 0.33    | 29.42±3.98                | 0.39    |
| Albumin (g/dL)                               | 3.84±0.54       | 3.83±0.64      | 0.91    | 3.81±0.68                 | 0.75    |
| Thyroid-Stimulating Hormone (μIU/mL)         | 3.37±9.87       | 1.65±1.01      | 0.57    | 1.88±1.07                 | 0.69    |
| Triglycerides (mg/dL)                        | 108.85±47.9     | 114.57±60.53   | 0.7     | 128.89±71.13              | 0.27    |
| Diagnostic group - no. (%)                   |                 |                |         |                           |         |
| Hypertension                                 | 223(85.11%)     | 29(56.86%)     | <0.01   | 28(73.68%)                | 0.08    |
| Diabetes Mellitus                            | 98(37.4%)       | 13(25.49%)     | 0.1     | 12(31.58%)                | 0.49    |
| Cardiovascular Disease                       | 38(14.5%)       | 5(9.8%)        | 0.37    | 5(13.16%)                 | 0.83    |
| p.N264K                                      | 5(1.91%)        | 2(3.92%)       | 0.38    | 2(5.26%)                  | 0.2     |
| Event - no. (%)                              |                 |                |         |                           |         |
| Composite Event                              | 145(55.34%)     | 6(11.76%)      | <0.01   | 3(7.89%)                  | <0.01   |
| Deceased                                     | 57(21.76%)      | 4(7.84%)       | 0.02    | 2(5.26%)                  | 0.02    |
| Kidney event                                 | 125(47.71%)     | 4(7.84%)       | <0.01   | 2(5.26%)                  | <0.01   |
| Follow-up time - yr                          | 6.67±3.5        | 7.19±2.8       | 0.31    | 7.42±2.77                 | 0.2     |
| Time to event - yr                           | 4.02±3.57       | 6.85±3.09      | <0.01   | 7.25±2.82                 | <0.01   |

CONFIDENTIAL

This material is the property of the University of Pennsylvania.

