**Appendix 3 Propensity score matching for all APOL1 high-risk and APOL1 low-risk cohort**

|                                              | APOL1 high-risk | APOL1 low-risk |         |                           |         |
|----------------------------------------------|-----------------|----------------|---------|---------------------------|---------|
|                                              |                 | Initial cohort |         | Propensity score matching |         |
| Number                                       | 1113            | 995            | P value | 912                       | P value |
| Age - yr                                     | 51.22±15.67     | 50.59±13.88    | 0.33    | 50.13±14.12               | 0.1     |
| Female - no. (%)                             | 701(62.98%)     | 646(64.92%)    | 0.35    | 593(65.02%)               | 0.34    |
| SBP - mmHg                                   | 129.09±18.3     | 129.47±17.47   | 0.63    | 129.48±17.47              | 0.63    |
| DBP- mmHg                                    | 77.04±12.02     | 77.59±11.47    | 0.28    | 77.56±11.54               | 0.32    |
| Body Mass Index - kg/m           | 31.95±7.8       | 32.05±7.86     | 0.77    | 32.31±7.85                | 0.31    |
| Hemoglobin A1c (%)                           | 6.59±1.81       | 6.35±1.35      | 0.04    | 6.39±1.38                 | 0.11    |
| Creatinine (mg/dL)                           | 1.14±0.68       | 0.88±0.3       | <0.01   | 0.89±0.3                  | <0.01   |
| Blood Urea Nitrogen (mg/dL)                  | 16.73±10.59     | 13.1±5.97      | <0.01   | 13.19±6.09                | <0.01   |
| eGFR - ml/min/1.73m              | 78.26±27.96     | 90.63±19.31    | <0.01   | 89.94±19.02               | <0.01   |
| UACR (IQR) - mg/g                            | 17.23(11-44)    | 15.31(12-24)   | <0.01   | 15.31(12-24)              | <0.01   |
| 30~299 - no. (%)                             | 163(14.64)      | 165(16.58)     |         | 149(16.34)                |         |
| ≥ 300 - no. (%)                              | 60(5.39)        | 29(2.91)       |         | 28(3.07)                  |         |
| Red Blood Cells (×10  /μL)       | 4.24±0.66       | 4.33±0.62      | <0.01   | 4.33±0.62                 | <0.01   |
| White Blood Cells (×10  /μL)     | 7.38±3.48       | 7.23±3.07      | 0.28    | 7.23±3.11                 | 0.3     |

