## **3 Cohorts, inclusion criteria, and analytic sets**

Primary derivation set (APOL1-HR, preserved eGFR):

Inclusion: APOL1 genotype = high-risk (two risk alleles: G1/G1, G2/G2, G1/G2), available plasma proteomics (SomaScan platform), baseline eGFR > 60 mL/min/1.73 m^2 measured at or 2 months before or 1 month after of sampling, available UACR (or imputed as specified).

Final sample size in derivation set:  $N = 851$ . Baseline descriptive statistics, event counts, and follow-up summaries are provided in manuscript. Key cohort summary (derivation APOL1-HR preserved-eGFR): mean age 49.2 years; female proportion 66.5%; mean eGFR 90.6 mL/min/1.73 m^2; median UACR 17.23 mg/g; composite event rate 17.98% ( $n = 153$ ); mean time to event 6.51 years; median follow-up 7.3 years.

Secondary analytic sets:

APOL1-HR with existing CKD at baseline: 262 participants included for comparison and benchmarking of APRS behavior in established disease.

APOL1-low-risk extension: an additional 995 participants to evaluate specificity and cross-genotype performance.

EUR comparison set (review-only):  $N = 514$  (used for method comparisons but not central to the APOL1-focused primary aims).

External validation cohorts

ARIC (Atherosclerosis Risk in Communities): African-ancestry subset with SomaScan proteomics (where available).

UK Biobank (UKB): African-ancestry subset with Olink proteomics (smaller targeted panels). Because platforms differ, apply the prespecified cross-platform mapping and multi-output imputation.

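### Appendix 3 is presented as a propensity-matched comparison of all APOL1 high-risk and low-risk participants, but it stacks two eGFR strata unweighted and remains unbalanced on four of seven matching variables

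*Combined protocol and SAP*

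**What the plan says.** Protocol section 3.2 gives the purpose of the matching as "To better enable comparison between the African ancestry APOL1 high-risk and low-risk groups". The propensity model uses seven variables: eGFR, UACR, age, sex, diabetes, hypertension and cardiovascular disease. The matching was done by stratum, "with separate matching performed for participants with eGFR >60 and ≤60". The section states no matching ratio, caliper, replacement rule, target population or balance criterion.

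Each appendix has one high-risk column, which does not change, and a low-risk column before and after matching. The low-risk group goes from 944 to 874 in Appendix 1 (eGFR >60), from 51 to 38 in Appendix 2 (eGFR ≤60), and from 995 to 912 in Appendix 3 (all participants). In Appendix 3 the eGFR row reads "78.26±27.96 | 90.63±19.31 | <0.01 | 89.94±19.02 | <0.01": high-risk, low-risk before matching with its P value, then low-risk after matching with its P value.

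SAP section 3 lists the low-risk participants as a secondary set, "an additional 995 participants to evaluate specificity and cross-genotype performance". Protocol section 3.1 places the primary analysis in high-risk people with eGFR >60.

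**The concern.** A table titled as propensity matching for the whole cohort invites the reader to compare its outcome rows as if baseline kidney function had been equalised. Appendix 3 shows composite events in 26.8% of high-risk and 15.1% of low-risk participants, P<0.01. If the groups differ mainly in how many people already had reduced eGFR, that contrast cannot be read as a genotype difference. Any cross-genotype comparison built on the pooled set would carry the same imbalance.

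The eGFR ≤60 stratum raises a second problem. After matching, its P values for eGFR, hypertension and sex are 0.07, 0.08 and 0.10, which look like balance. With 38 low-risk people, P values in that range are compatible with substantial residual differences.

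**Working it through.** **Inputs** (Appendices 1 to 3, high-risk vs matched low-risk)

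| | eGFR >60 | eGFR ≤60 | Pooled |
|---|---|---|---|
| N | 851 vs 874 | 262 vs 38 | 1113 vs 912 |
| eGFR, mean±SD | 90.59±17.04 vs 91.96±16.39 | 38.19±16.67 vs 43.46±15.97 | 78.26±27.96 vs 89.94±19.02 |
| Composite events | 153 vs 135 | 145 vs 3 | 298 vs 138 |

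**Step 1. Reproduce Appendix 3 from Appendices 1 and 2.**
- High-risk mean: (851×90.59 + 262×38.19)/1113 = 78.26.
- Matched low-risk mean: (874×91.96 + 38×43.46)/912 = 89.94.
- Combining within- and between-stratum variation gives SDs of 27.96 and 19.02.
- Events: 153+145 = 298 and 135+3 = 138.

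All agree with Appendix 3. It is the two strata added together, with no separate match and no weights.

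**Step 2. Balance on eGFR.** Standardised mean difference (SMD) = difference / √((SD₁²+SD₂²)/2).
- Pooled, before matching: (78.26−90.63)/√((27.96²+19.31²)/2) = −0.51.
- Pooled, after matching: (78.26−89.94)/√((27.96²+19.02²)/2) = −0.49.
- eGFR >60, after matching: −1.37/16.72 = −0.08.
- eGFR ≤60, after matching: −5.27/16.32 = −0.32.

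**Step 3. The other matching variables, after matching.**

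| SMD | eGFR >60 | eGFR ≤60 | Pooled |
|---|---|---|---|
| Age | −0.05 | 0.15 | 0.07 |
| Female | 0.03 | −0.29 | −0.04 |
| Hypertension | 0.03 | 0.29 | 0.13 |
| Diabetes | 0.085 | 0.12 | 0.13 |
| Cardiovascular disease | −0.075 | 0.04 | −0.035 |

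UACR is reported only as median and IQR, so no SMD can be formed. Its matched P value is 0.05 in Appendix 1 and <0.01 in Appendix 3.

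**Step 4. Source of the pooled gap.** The share with eGFR ≤60 is 262/1113 = 23.5% in the high-risk group and 38/912 = 4.2% in the matched low-risk group. The part due to stratum mix is the difference in shares times the difference between the average stratum means: (0.2354−0.0417)×(40.825−91.275) = −9.77. That is 84% of the −11.68 gap. The remaining −1.91 lies within strata.

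**Step 5. Composite outcome on a common mix.** Stratum rates are 17.98% vs 15.45% (eGFR >60) and 55.34% vs 7.89% (eGFR ≤60).

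| Share with eGFR ≤60 | High-risk | Low-risk | Gap (points) |
|---|---|---|---|
| As tabulated (23.5% vs 4.2%) | 26.8% | 15.1% | 11.6 |
| Low-risk mix, 4.2% in both | 19.5% | 15.1% | 4.4 |
| Pooled mix, 300/2025 = 14.8% in both | 23.5% | 14.3% | 9.2 |
| High-risk mix, 23.5% in both | 26.8% | 13.7% | 13.1 |

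For example, the high-risk rate at the low-risk mix is 0.1798×(1−0.0417) + 0.5534×0.0417 = 19.5%. Within eGFR >60 alone the gap is 2.5 points (P=0.16 in Appendix 1).

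**Step 6. Does weighting repair the pooled set?** Weighting the low-risk group to the high-risk mix gives a mean eGFR of 0.7646×91.96 + 0.2354×43.46 = 80.54. The gap is then −2.28 (SMD −0.08). Weighting the high-risk group to the low-risk mix gives 88.41 against 89.94, a gap of −1.53. In the first case each of the 38 low-risk people carries weight 0.2354/0.0417 = 5.65 and each of the 874 carries 0.7646/0.9583 = 0.80. The effective low-risk sample is 912²/(874×0.798² + 38×5.65²), or about 470.

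**The case against.** The strongest reply is that the analysis that matters is already sound. The primary population is eGFR >60, matching there was done and reported separately, and every matching variable with a computable SMD is below 0.1. This stands. A reader might infer that the cross-genotype question cannot be answered at all, or that the eGFR >60 stratum must be matched again. The reported figures support neither; only the crude pooled comparison fails.

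It can also be said that retaining every high-risk participant and pruning controls is a legitimate design, and that equal group sizes are not required. That stands too. The fault is pooling strata with very different mixes and no weights.

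Third, no section names Appendix 3 as the source of an effect estimate, and none claims that the APRS is specific to APOL1 disease. SAP section 3 cites 995 low-risk people, the unmatched total, so the matched 912 may not feed that evaluation. Discrimination within the low-risk group needs no covariate matching to the high-risk group. Appendix 3 also prints its P<0.01 values openly. These points limit the consequence. They do not make the table a matched comparison.

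Two further inferences are tempting. One is that the pooled outcome gap is CKD mix and not genotype. The standardised gap can be smaller or larger than the crude one, so the data do not settle this. The other is that low-risk people with eGFR ≤60 were selectively sampled, because their composite rate before matching (6/51, 11.8%) is below that of low-risk people with eGFR >60 (142/944, 15.0%). The exact 95% interval for 6/51 is 4.4% to 23.9%, Fisher's P is 0.69, and no sampling rule in the documents points that way.

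**Conclusion.** Wrong as written, in a secondary analysis; not a must-fix. The pooled comparison in Appendix 3 is not matched: four of the seven matching variables still differ at P<0.01, and the pooled eGFR SMD improves only from −0.51 to −0.49. The crude 11.6-point composite gap has no clean genotype reading. On a common stratum mix it runs from 4.4 to 13.1 points, and the upper end depends on a low-risk stratum with 3 events.

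The eGFR ≤60 comparison is also inadequately balanced, with SMDs near 0.3 for eGFR, sex and hypertension. It is too small to support any statement on APRS performance or specificity in low-risk people. The eGFR >60 comparison can stand, subject to UACR, for which no SMD can be formed.

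These figures rest on published means, SDs and counts. Overlap of propensity scores within strata cannot be examined without individual data. The standardised gaps use crude event proportions and ignore differences in follow-up. APRS derivation, testing and external validation are unaffected.

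**What to change.** In protocol section 3.2 and the appendices:

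- Name the eGFR >60 stratum (Appendix 1) as the matched cross-genotype comparison. It need not be matched again.
- Do not present or use Appendix 3 as matched unless both groups are weighted to a common eGFR distribution. If it is weighted, state the target distribution and report balance within each stratum as well, because a pooled SMD of −0.08 would conceal −0.32 in the eGFR ≤60 stratum. Otherwise retitle it as an unadjusted description of the combined strata.
- Judge balance by standardised differences, with a threshold of 0.1, and not by P values. Include log-transformed UACR.
- State the matching ratio, caliper, replacement rule and target population.
- Label the low-risk set with eGFR ≤60 (38 people, 3 events) descriptive, and draw no APRS performance or specificity claim from it.

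The cost is a little re-analysis of data in hand and some rewording. The pooled contrast either loses precision (an effective low-risk sample of about 470 instead of 912 if weighted to the high-risk mix) or is dropped.

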#### 3.3 ARIC Study (Validation Cohort)

The Atherosclerosis Risk in Communities (ARIC) Study is a prospective U.S. cohort of men and women (15,792 participants at baseline, 1987–1989). For validation, we will use African-American ARIC participants with APOL1 high-risk genotype. Specifically, 314 African-American APOL1 high-risk individuals who attended visit 2 (1990–1992) were included. An additional 2021 African-American individuals with APOL1 low-risk genotype and 8,602 European ancestry APOL1 low-risk participants were included as external reference. Genotyping (TaqMan assays) and SomaScan proteomics (5K proteins) were available on visit-2 samples. Follow-up (ascertainment of outcomes) is truncated at 10 years from

visit 2 to harmonize with the PMBB analysis. All ARIC analyses were approved under study application MP4524.

### **3.4 UK Biobank (Validation Cohort)**

The UK Biobank (UKB) is a large cohort of ~500,000 U.K. adults (ages 40–69 at enrollment, 2006–2010). We will validate APRS among UKB participants of African ancestry. Plasma proteomics were measured by the Olink platform in ~50,000 participants. Of these, 1,171 were of African descent, including 204 APOL1 high-risk individuals. Olink measurements will be log2-transformed and normalized; missing proteins (compared to SomaScan) will be imputed via multi-output penalized regression trained on PMBB data. Outcomes (eGFR, dialysis/transplant, mortality) are ascertained via linked clinical and registry data. Analyses are conducted under UKB Resource Application #273810.

### **3.5 Participant Eligibility**

**Inclusion Criteria:** Adults ( $\geq 18$  years) of genetically inferred African ancestry with APOL1 high-risk genotype (two risk alleles: G1/G1, G2/G2, or G1/G2); baseline eGFR  $> 60$  mL/min/1.73m^2; available baseline plasma proteomics; and at least one follow-up record (eGFR or relevant outcomes).

**Exclusion Criteria:** Prevalent end-stage kidney disease at baseline (on dialysis or prior kidney transplant); missing or ambiguous APOL1 genotype; failed proteomic assay; or insufficient key data for analysis.

